##### Post-Introduction of SBIRT

Focus Group Discussions -Focus group discussions will be conducted with Lay Health Worker Case Managers and Nurse Prescribers concerning challenges to implementing the intervention and its integration with HIV care. Focus group discussions are ideal for identifying normative understanding following the generation of multiple perspectives. The sample size for each study group category anticipates what is required to reach saturation on key themes but may be supplemented if necessary.

##### Semi-structured Interviews

During their final study visit at week 24, participants will be asked to participate in a semi-structured interview. For participants who were unable to quit smoking in the course of their participation in the study, the reasons for this will be explored. For participants who quit and resumed smoking, the factors that prevented them from staying smoke free will be explored. For participants who were successful in quitting, the factors that enabled them to quit successfully will be identified.

#### **5. Training of LHWs, Nurse dispensers, and research assistants**

##### Training of LHWs on standard of care

LHWs will undergo a two-day onsite training on providing standard of care. This will be provided to them by the study coordinator, the data manager, and the research assistant assigned to the site. They will also be trained on how to fill the screening tool.

##### Training of LHWs on SBIRT

LHWs will receive formal training on SBIRT which will take three days and will emphasize interactive activities such as roleplaying. To ensure sufficient assimilation of training materials, LHW case managers must pass a post-training examination. The 5“A”s already has established theory-informed and

evidence-supported methods and strategies to achieve behavior change. New training materials and revisions to the existing LHW case manager standard operating procedures will be piloted.

#### Training of Nurse prescribers/dispensers on varenicline use

Nurse prescribers will attend a three-day didactic and hands-on centralized training on the SBIRT intervention and how to integrate it into their current work at sites. They will receive specialized training on the treatment component of SBIRT – varenicline use. They will be taught how to screen participants for their eligibility to receive varenicline, how to prescribe it and how to monitor participant adherence and side-effects. They will also receive training on the tools they need to complete -the adherence tool and adverse events tool.

In-service training will be conducted for all licensed clinicians eligible to prescribe varenicline - the nurse prescribers/dispensers, which will be scheduled and led by [name] but provided by Implementation leaders. The in-service will provide the background and orientation to treatment with varenicline. These in-service trainings will be repeated at each clinic (at different days and times) to accommodate diverse staff schedules.

#### Training of Research Assistants

Research Assistants will undergo a two-week training before they commence work on the BSMART study. They will be trained on the following:

- Research ethics training which includes the Collaborative IRB Training Initiative certification (CITI)
- Good clinical practice
- the study protocol, eligibility and consenting processes,
- how to provide the standard of care intervention,
- CO monitoring
- how to fill the required data collection tools using REDCap and
- how to administer semi-structured interviews to participants

They will attend the training sessions for LHWs and Nurse prescribers on SBIRT.

## **6. Constituting consultation groups**

Consultation groups will be established to address questions clinicians may have when prescribing varenicline.

## **7. Participant sampling and recruitment:**

Recruitment activities will begin at the HIV care services through introduction of the study by the LHW Case Managers. Tobacco use screening will occur within the context of HIV outpatient care. The LHW Case Manager will identify individuals who initially screen positive for tobacco use. The LHW case manager will apply the study eligibility criteria and participants found to be eligible for the study will be linked with the research assistant stationed in the HIV clinic and working closely with the LHW case manager. Individuals who present at the study clinic for screening and are eligible will complete the informed consent process on a first come, first serve basis prior to the completion of any study specific activities. We will ensure ethical conduct of the study through respecting and protecting the interests of all potential and enrolled participants, building trust between researchers and participants, and conducting the study under the principles of good clinical and laboratory practices. Informed consent will be administered in the participant's choice of English or Setswana language by trained research assistants.

## **Randomization methods**

We have chosen 15 (and 4 reserved) high-volume (>1000 HIV-positive patients currently active and on ART) health facilities (See Figure 4) in the ABLE project for inclusion based on numbers of patients, accessibility to the research team, and willingness to collaborate. After a baseline period of 1 year, the BSMART intervention will be implemented in a step of five new randomly selected sites (1 district hospital, 2 primary hospitals, 2 primary care clinics) until it is eventually implemented in all 3 steps (15 sites). A computer-generated list containing facilities stratified by type will determine the order in which the sites receive the intervention. The randomization list will be maintained by a statistician who is not involved in the study, and the site allocation will remain concealed from the research team and clinical teams throughout the study and will be revealed for a given step only 1 month before the implementation of the intervention to allow for training.

[figure not shown]

Figure 4: Selected and reserve facilities for BSMART project

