## Methods

### Study Design

We will utilize a stepped wedge cluster randomized trial to implement BSMART. BSMART will be sequentially rolled out to 15 participating HIV treatment and care facilities assigned in three steps (Table 1). Each step will provide data for a 12-month control/pre-implementation, a 12-month implementation, and a 12-month maintenance period. We will stratify Botswana's HIV treatment and care facilities into three levels of facilities. We will randomly assign each of the three levels of facilities to one of three study steps. Each step will comprise (i.e. have representation) from three levels of facilities, giving each level of facilities the same probability of beginning the intervention at any step). We choose this design to:

- 1) minimize the practical, logistical, and financial constraints associated with large-scale project implementation,
- 2) control for the effect of time, and
- 3) ensure that all HIV treatment and care practices will eventually offer the intervention and assess maintenance.

The study will screen approximately 6,900 HIV-infected patients and we expect to enroll 750 eligible participants, 375 of whom will participate in the pre-implementation phase and 375 of whom will participate in the implementation phase across three waves of implementation at five facilities each.

| Table 1: Time Periods for Stepped Wedge Implementation |                                                  |         |                |                |                |             |
|--------------------------------------------------------|--------------------------------------------------|---------|----------------|----------------|----------------|-------------|
| Steps                                                  | Total Number of Participants                     | Year 1  | Year 2         | Year 3         | Year 4         | Year 5      |
| 1                                                      | 5 facilities, n=250 PLWH (1DH, 2 PHs, 2 clinics) | Control | Implementation | Maintenance    |                |             |
| 2                                                      | 5 facilities, n=250 PLWH (1DH, 2 PHs, 2 clinics) |         | Control        | Implementation | Maintenance    |             |
| 3                                                      | 5 facilities, n=250 PLWH (1DH, 2 PHs, 2 clinics) |         |                | Control        | Implementation | Maintenance |

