## Study Population

Participants will be drawn from the population of HIV-infected patients receiving care at 15 selected health facilities that are part of the Accelerating Botswana through the Last Mile to Epidemic Control (ABLE) project. We plan to screen approximately 6,900 HIV-infected patients (230 PLWH per facility per year) for tobacco smoking and subsequently identify 750 patients who are interested in quitting into the trial, a total of 375 of whom will participate in the control period and 375 of whom will participate in the implementation period across three waves of implementation at five facilities each. Study participants will receive HIV care and treatment according to national standards.

Eligibility criteria: To maximize “real world” practice we attempted to err on the side of inclusivity in the study’s eligibility criteria. We will apply the following inclusion criteria:

- (1) HIV-infected,
- (2) self-reported current daily smoker,
- (3) age 18 years and older,
- (4) engaged in HIV care as defined by being on ART for at least 6 months at one of 15 selected health facilities (or four reserve facilities), and
- (5) willing/able to provide informed consent in English or Setswana.

We will apply the following exclusion criterion:

- (1) pregnancy or nursing

We acknowledge that patients living with HIV/AIDS in real-world treatment settings use other substances in addition to tobacco and will often have some problems associated with that use. To limit this study to those who smoke tobacco only means tailoring the intervention to a small group that is not truly representative of the larger population of PLWH.

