## Power and Sample size

Our sample size is based on the hypothesis that interventions will have a substantial impact on primary endpoints compared to the control phase (Figure 5).

**Main effect:** Based on a meta-analysis of 24 randomized controlled trials in LMIC, smoking abstinence at 6 months follow-up ( $P_{\text{control}}$ ) for usual care averages 10% (range, 8% to 14%). Assuming withdrawal from trial follow-up or loss to follow-up to be 5%, our sample of 25 PLWH per cluster per period has power of 87% to detect at least 10% increase (main effect,  $\Delta = (P_{\text{implementation}} - P_{\text{control}})$ ) in the primary endpoint at six months with the assumption that the event rate for those in control phase is 10% and two-sided alpha at intra-cluster correlation of 0.02.

[figure not shown]

Fig 5. Power to detect primary endpoint, main effect versus standard of care (SOC)

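### The stated 1-month concealment of each facility's step cannot operate, because Table 1 makes the crossover date evident about 12 months ahead, at the start of the facility's control year

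*Protocol*

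**What the plan says.** Under Randomization methods, an independent statistician holds the list, "the site allocation will remain concealed from the research team and clinical teams throughout the study", and the allocation "will be revealed for a given step only 1 month before the implementation of the intervention to allow for training".

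The Study Design section fixes the periods: "Each step will provide data for a 12-month control/pre-implementation, a 12-month implementation, and a 12-month maintenance period". The table there ("Table 1: Time Periods for Stepped Wedge Implementation") places them in calendar time. Step 1 is control in Year 1 and implementation in Year 2, Step 2 is control in Year 2 and implementation in Year 3, and Step 3 is control in Year 3 and implementation in Year 4. The cells before a step's control year are empty.

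On entry to the trial, the recruitment section says: "The LHW case manager will apply the study eligibility criteria and participants found to be eligible for the study will be linked with the research" (the sentence goes on to name the staff member who takes consent). The intervention section gives the same cadre of lay health workers the later task of delivering the brief intervention and referring participants for varenicline. Control participants receive a brochure.

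**The concern.** In an open cluster trial that enrols new people in each phase, hiding the crossover date from recruiting staff protects against selection at entry. The protocol claims that protection, and a reader of the results would rely on it. If staff know from the start of the control year when counselling and free varenicline will arrive, a motivated smoker seen late in that year can be asked to come back. That lowers control abstinence and raises implementation abstinence without any treatment effect. The primary comparison of 6-month abstinence is exposed directly.

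**Working it through.** **1. Can the stated 1 month be reproduced?** Lead time = month of crossover minus month when the facility's own control phase starts, both from Table 1 and counted from the start of Year 1.

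| Step | Control starts | Crossover | Lead time | Stated |
|---|---|---|---|---|
| 1 | 0 | 12 | 12 | 1 |
| 2 | 12 | 24 | 12 | 1 |
| 3 | 24 | 36 | 12 | 1 |

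It cannot be reproduced for any step.

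**2. Does each facility really recruit only in its own two years?** The totals confirm it. Screening is "230 PLWH per facility per year", and 230 × 15 facilities × 2 years = 6,900, the stated number. Enrolment is 25 × 15 × 2 = 750, also as stated. A facility waiting for its control year recruits nobody, so the start of control activity is itself the disclosure. That start is visible on site: workers are trained in the standard of care and a research assistant is assigned. Step 1 staff are also brought into a pre-implementation workshop, and the Study timeline puts the adaptation focus groups in Year 1, quarters 2 and 3.

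**3. How large could the bias be? (illustration only)** The planning inputs are "our sample of 25 PLWH per cluster per period has power of 87% to detect at least 10% increase", with "the event rate for those in control phase is 10" per cent, ICC 0.02 and 5% loss. The alpha level is not printed, so 0.05 two-sided is assumed.

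- Effective number per phase: 375 × 0.95 / (1 + 22.75 × 0.02) = 356.25 / 1.455 = 244.8.
- Anchor: with this number, power for 10% against 20% is 87.5%, in line with the stated 87%.

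The following are assumed and are not in the protocol. Half of enrolees are ready to quit. Quit rates without any BSMART effect are 15% if ready and 5% if not, which average to the plan's 10%. For m months before crossover every ready smoker is deferred, a non-ready one takes the place, and the deferred smoker takes a non-ready place after crossover.

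The share of places affected is s = (m/12) × 0.5. Control rate = 5% + 10% × (0.5 − s). Implementation rate = 5% + 10% × (0.5 + s).

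| m | s | Control | Implementation | Spurious difference | After dropping controls of the last 90 days |
|---|---|---|---|---|---|
| 1 | 0.042 | 9.58% | 10.42% | 0.8 points | 0.4 points |
| 3 | 0.125 | 8.75% | 11.25% | 2.5 points | 1.25 points |
| 6 | 0.25 | 7.50% | 12.50% | 5.0 points | 4.2 points |

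The last column uses the exclusion already planned against contamination. For m = 1 and m = 3 it returns controls to 10%. For m = 6, 6.25 of the remaining 18.75 controls per facility are ready, so the control rate is 5% + 10% × 6.25/18.75 = 8.33%. In every row the deferred smokers stay in the implementation group. The differences scale with the share deferred: if half of ready smokers are deferred, the 3-month figure is 1.25 points, and with no deferral it is zero.

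**4. What would an implementation-side exclusion add?** For m = 3, a facility fills 25/12 × 3 = 6.25 places in its first 90 days after crossover. If the deferred smokers enter then, these places hold 3.125 ordinary ready and 3.125 deferred smokers. The remaining 18.75 places are half ready, so the implementation rate is 10%, against 10% in the trimmed controls. The spurious difference disappears under these assumptions.

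**The case against.** The strongest reply is that the conflict is one of wording and that the harm is conjecture. Much of this stands.

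- **Nothing in the protocol describes deferral.** Consent follows order of arrival, and the Appendix B1 screening form has no readiness item. Stage of change and the readiness ruler are recorded by the research assistant at enrolment in both phases, so an imbalance could be seen afterwards. However, the order of consent applies only once a patient has been brought forward, and a worker can judge motivation without a form.
- **A reader might infer a large surplus of smokers to choose from**, by applying the quoted regional smoking prevalence of 12.5–44.3% to 230 screened (about 29 to 102). The documents do not support this. That is general smoking prevalence, while entry needs daily smoking, at least 6 months on ART, no pregnancy or nursing, and consent. The planned yield is 25 of 230 (10.9%), exactly the target. At 12.5% prevalence, 25 of 28.75 (87%) would have to be eligible and agree. The replacement assumed in the illustration is therefore not assured.
- **A reader might infer 24 months of warning for Step 3**, known by elimination once Step 2 opens at month 12. Those sites enrol nobody in Year 2 and can defer nobody then, and the four reserve facilities blur the elimination. The usable lead is 12 months.
- **A reader might infer a false-positive rate of about 15% (3 months) or 46% (6 months) instead of 5%.** The effective numbers above do give these figures, but only with the assumed readiness and quit rates and full deferral at every facility. With the planned 90-day control exclusion the 3-month figure is about 7%. An assumption that half are not ready also sits poorly with the Study Population text, which describes enrolling people interested in quitting.
- **The Randomization methods text could be read as one common baseline year.** Table 1 and both totals contradict that. Even then, Step 3 would be known about 13 months ahead, once Step 2 was named at month 23.

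None of this rescues the 1-month statement.

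**Conclusion.** The concern holds as an internal contradiction that removes a stated safeguard. Under Table 1 a facility's step and crossover date are evident to its staff about 12 months ahead, against the 1 month claimed, at all 15 facilities. This rests only on the protocol's own schedule and totals.

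The resulting bias is a possibility, and its size cannot be derived from the documents. The 2.5 points for 3 months of deferral, and 1.25 points after the planned control exclusion, depend on assumed readiness, quit rates and complete deferral. They show the direction and that the planned sensitivity analysis covers only half of the route. They are not an estimate of what will happen, and they do not show an inflated error rate for this trial.

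**What to change.** 1. **Reconcile the concealment statement with Table 1.** State that the step is known from the start of the facility's control year, and have the independent statistician release each step's facilities only shortly before that year. This makes the claim true. It does not hide the crossover date, so the next two changes are needed as well.
2. **Fix the enrolment rule.** State that all consecutive eligible smokers are offered enrolment within each recruitment window, in both phases. A fixed monthly quota is not advised, because the Study timeline shows recruitment in three-quarter blocks with gaps.
3. **Extend the 90-day sensitivity analysis to the implementation side.** Besides the late controls, drop implementation enrolees from the first 90 days after crossover. Also drop those already identified as daily smokers at the same facility during its control year, using the dated Appendix B1 screening forms.

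The cost is protocol wording, a release schedule for the existing list, and additional sensitivity analyses on data already collected. Sample size does not change. The downside is that these analyses use fewer participants and will be less precise than the primary analysis.

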## Participant Timelines - Control Phase

### Informed consent

#### Study Participants (People living with HIV who smoke)

Individuals who present at the study clinic will be screened for study eligibility. Those found to be eligible will be linked to a research assistant stationed within the same clinic who will lead them through the informed consent process and then offer enrollment to those interested in participating in the study. The informed consent process will be completed on a first come, first served basis prior to the completion of any study specific activities. A research assistant will provide a printed version of the signed informed consent to each participant as well as any study information the participant requests to have printed. The written consent will be provided in the participant's choice of English or Setswana and administered by trained research assistants. Research assistants will review the document with each participant in a private environment, respond to questions, and emphasize participant rights regarding research participation. Research assistants will use assessment tests in the consent process to ensure that the participants comprehend the study and are able to provide informed consent. The ability to provide informed consent is one of the inclusion criteria for this study. Participants will have the right to withdraw participation at any time, without interruption to their health and HIV care and treatment services rendered at the health facility.

### Enrollment in BSMART study

At enrollment, research assistants will fill the demographic form, intake smoking history questionnaire and use the stages of change algorithm and readiness ruler to determine the individual's stage of change for quitting. Lay Health worker case managers will provide participants with the standard of care brochure which contains basic information on the risks of smoking and the need to stop smoking.

### Follow-up

Research assistants will fill out follow-up smoking questionnaires at weeks 4, 12 and 24 after the patient receives the SOC brochure. Participants will be provided with breath CO measurements using CO Check+

(coVita) at baseline and then weeks 12 and 24 after enrollment. Participants will also be asked to respond to a semi-structured interview at week 24 that explores challenges to smoking cessation, barriers experienced by participants and reasons for success in those who were able to quit successfully.

| Table 2: Participant Timeline- Control Phase |                    |                                           |        |         |         |
|----------------------------------------------|--------------------|-------------------------------------------|--------|---------|---------|
|                                              | Responsible person | 1 st clinic visit/
Baseline | Week 4 | Week 12 | Week 24 |
| Screening of participants                    | LHW case manager   | X                                         |        |         |         |
| Informed Consent                             | Research Assistant | X                                         |        |         |         |
| Enrollment in BSMART study                   | Research Assistant | X                                         |        |         |         |
| Intake Smoking Questionnaire                 | Research Assistant | X                                         |        |         |         |
| Receipt of SOC brochure                      | LHW case manager   | X                                         |        |         |         |
| Follow-up smoking questionnaire              | Research Assistant |                                           | X      | X       | X       |
| Stages of change                             | Research Assistant | X                                         | X      | X       | X       |
| Breath CO                                    | Research Assistant | X                                         |        | X       | X       |
| Semi-structured Interview                    | Research Assistant |                                           |        |         | X       |

